## Abstract

**Background:**

Inadequate nutrition and a lack of physical activity contribute to functional decline and complications from chronic diseases in older adults. The pandemic halted or altered necessary Older Americans Act (OAA) nutrition services provided to vulnerable, community-dwelling older adults in San Antonio, Texas. The “digital divide” or gap in technological access and knowledge further heightened the detrimental effect of the COVID-19 pandemic on older adults who may be “digitally excluded” from social, economic, and health-related interactions. During the pandemic, San Antonio congregate meal sites funded by OAA remained partially open biweekly to distribute meals but no longer offered in-person nutrition education, physical activity classes, and social activities. This project expands the current congregate meal programming infrastructure and partnerships with Older Adults Technology Services (OATS) to create a sustainable approach focused on improving the health of older adults.

**Objective:**

The study aims (1) to test the impact of a digital nutrition education intervention on the primary outcomes of food security and diet quality; (2) to determine the effect of the intervention on secondary outcomes of technology knowledge and usage, physical activity, and social isolation and loneliness; and (3) to examine the long-term impact and sustainability of technology use on food security, diet quality, physical activity, social isolation, and loneliness.

**Methods:**

This proposed digital nutrition education intervention study targets technologically limited older adults enrolled in the congregate meal program (CMP) using a stepped-wedge clustered randomized controlled trial. Key community partners, City of San Antonio Department of Health Services Senior Services Division and OATS, contributed to the study’s planning phase, research design, and implementation. The 20-week intervention included 5 weeks of in-person technology training, including internet access and technical support for 1 year and devices, followed by 15 weeks of a culturally tailored online nutrition education intervention. The study randomized 398 older adults from 12 congregate meal sites. Data collection took place at baseline, 3 months, 6 months, 9 months, 12 months, and 18 months. If successful, the impact of this program could be applied throughout the national OATS network and to similar CMPs to bridge the digital divide beyond the COVID-19 pandemic.

**Results:**

Recruitment and enrollment of 398 older adults at 12 CMPs was completed in December 2022. Study CMPs were randomly assigned to Cohort 1 and 2: 164 completed Cohort 1 in August 2023 and 111 completed Cohort 2 in April 2024. Eighteen-month data collection is ongoing.

**Conclusions:**

This study aims to determine the impact of a digital nutrition intervention on older adults’ nutrition status, physical activity, loneliness and isolation, and technology access and usage. Results from this study can inform future interventions with vulnerable populations and may serve as a basis for other OAA nutrition services.

## Introduction

According to the 2020 population estimates from the Census Bureau, the fastest-growing demographic consists of adults aged 65 years or older, totaling over 55 million nationwide. Texas has a large number of older adult residents (3.9 million), second only to California and Florida [1]. Nutrition is essential for healthy aging [2], the maintenance of health, and the prevention of chronic diseases. However, older adults are at an increased nutritional risk due to a unique set of circumstances that encompasses physiological, cognitive, and social factors, including loneliness, depression, lack of money for food and access to food, and physical impairments that hinder food procurement and preparation [3]. Factors such as food insecurity and malnutrition contribute to suboptimal nutrition and elevate the risk of chronic diseases [4]. Research indicates that food insecurity rates among older adults can be as high as 20% [5], with malnutrition rates reaching 27% among community-dwelling older adults [5,6]. Poor diet quality has been correlated with diminished functional capabilities, heightened susceptibility to falls [7], frailty [8], and increased mortality [9]. Therefore, addressing food security among older adults at risk is imperative for enhancing dietary standards, preventing malnutrition and its associated ramifications, and managing chronic conditions.

The goals of the congregate meal program (CMP) funded by the Older Americans Act (OAA) are to reduce hunger and food insecurity, promote health and socialization, and delay adverse health effects so community-dwelling older adults 60 years or older may remain independent in their homes, reducing institutionalization [10]. Socialization at congregate meal centers provides mental well-being benefits in addition to nutritional benefits. The CMP serves lunchtime meals for up to 5 days per week to over 1.5 million older adults in the United States and served over 60,000 older adults in Texas in 2018 [11]. Although the CMP meals provide one-third of the dietary reference intakes, allow for higher intakes of certain nutrients, and contribute to overall higher diet quality compared to nonparticipants, nutrient inadequacies still exist, especially among lower-income participants [12]. Gaps in technological access and knowledge referred to as the “digital divide” [13] disproportionally affect older adults, those who live in rural areas, the disabled, and the impoverished populations [14]. The COVID-19 pandemic heightened the awareness of the digital divide and deepened inequities in vulnerable populations [15]. In addition, the COVID-19 pandemic amplified existing challenges for older adults in maintaining their health. Marginalized and vulnerable older adults experiencing poverty, chronic conditions, financial instability, and limited technology access and knowledge before the pandemic shouldered much of the pandemic burden and risk [16-19]. Importantly, at-risk community-dwelling older adults who attend congregate meal sites lack digital nutrition interventions to address deficits in suspended services [20]. Eating alone is a nutritional risk factor and is associated with reduced food intake [21] and risk for malnutrition. With centers closed, those individuals who live alone are impacted by social isolation to a greater extent, and providing an online social environment during meal times can alleviate this risk factor and could potentially improve nutrient status. Thus, improving technology access and knowledge and delivering a virtual nutrition intervention can extend beyond the constraints of CMP participants to other vulnerable older adult populations. Although online services may never fully replace in-person interactions, the overall reliance and dependency on technology have become an integral part of our society.

Successful dietary behavioral change interventions with older adults have common features including using behavior change theories to promote self-efficacy, containing clear and repeated messages, incorporating incentives for motivation, and sufficient contact [22,23]. Positive behavior change has successfully increased fruit and vegetable intake and fiber in interventions targeting community-dwelling older adults [24]. Interventions at congregate meal sites have successfully increased participant fruit and vegetable intake after a 5-session program [25] or a 4-week intervention [26]. Additional studies have documented improvements in nutrition risk scores, a small improvement in food-related behaviors for both congregate and homebound meal participants [27], and improvements in dietary supplement knowledge and behaviors in congregate meal participants [28].

Limited studies on digital interventions for older adults impacting nutrition exist, and published studies focus on eHealth or Telehealth [29,30] and disease-specific interventions [31-35]. Successful digital interventions have been documented using “telemonitoring” for 4 months to improve nutritional status and increase vegetable, fruit, and dietary fiber intake in a Dutch population [30]. This study observed a high level of participant satisfaction, with an 80% completion rate. The majority of dropouts were older and had poorer cognition and physical function [29]. Another telemedicine intervention had positive outcomes of reduced malnutrition and improved protein intake [33]. In interventions targeting specific disease states, evidence supports “eHealth” interventions using the web and mobile-based technologies to improve diabetes care [34], and an 8-week program to increase calcium intake and exercise to improve bone health [35].

Therefore, to test the impact of a technology-based intervention on the primary outcomes of food security and diet quality, we hypothesize that older adult participants will report improved overall nutrition quality and a reduction in food security (Aim 1). To determine the effect of the intervention on secondary outcomes of technology knowledge and usage, physical activity, social isolation, and loneliness, we hypothesize that providing access and training to technologically disadvantaged older adults will increase accessibility, knowledge, and improved attitudes toward technology use (Aim 2). To examine the long-term impact and sustainability of technology use on food security, diet quality, physical activity, and social isolation, we will evaluate the sustainability of online programming integrated into the CMP, assessed via surveys and usage data (Aim 3).

## Methods

### Design

This study is a closed cohort stepped wedge design in which the timing of the intervention is randomized by cluster, with the sequential crossover of clusters from control to intervention until all clusters have received the intervention. With this design, each cluster contributes data when they are participating in the intervention and when they are not. Stepped wedge designs are useful for several reasons. First, they allow all participants to receive the intervention, and each intervention arm can serve as its control, which decreases the number of units needed. Second, the design is practical in a situation with limited resources where the intervention logistically cannot be carried out all at once. Third, the design allows researchers to examine any effects of time on the intervention’s effectiveness [36,37]. Baseline data on current dietary intake, food security, malnutrition, technology use and attitudes, physical activity, social isolation, loneliness, and demographics were collected from all participants at Time 0. Each of the 12 centers was randomly assigned to one of 2 cohorts. Participants in Cohort 1 received the intervention first. Once Cohort 1 participants finished the intervention, a crossover occurred as Cohort 2 participants began the intervention. At the 12-month time point, the second cohort completed the intervention. Data will be collected for both groups each time point from T0 to T3 (Figure 1).

**Figure 1. F1:**
[figure not shown]
Stepped wedge cluster randomized trial schema depicting the staggered introduction of the intervention across clusters over time.

### Recruitment and Procedures

#### Study Setting and Sample

Fifty-two congregate meal sites associated with the Department of Health Senior Services in San Antonio serve approximately 2400 older adults, 60 years or older in San Antonio. The sites vary by geographical location, services offered, number and demographics of older adults served, and setting. The comprehensive city-provided centers include meal service, exercise rooms and equipment, classes of varying topics from nutrition to crafts to technology, social activities, and other supportive services related to health care needs. Early in the pandemic, the congregate meal sites condensed to 11 main “hubs” that provided frozen meals twice per week to nearly 2000 older adults. Activity booklets distributed with the meals monthly provide nutritional educational materials, but this does not replace the lack of curriculum and resources normally available. San Antonio CMP participants are 73 years old, 63% female, and 70% Hispanic. Among them, 33% are categorized as impoverished based on national poverty income levels, and 15% are considered at high nutritional risk based on the DETERMINE (Disease, Eating Poorly, Tooth Loss, Economic Hardship, Reduced Social Contact, Multiple Medications, Involuntary Weight Loss, Needs Assistance, and Elderly Status) your risk nutritional screen, used to assess nutrition risk for all OAA nutrition services programs in Texas.

Participants were recruited from a total of 14 CMP sites. Flyers were used to advertise the study and information sessions. The research team conducted a comprehensive information session at each site, using a presentation describing the study’s purpose, research methods, specific data to be collected, and reviewing the consent form. Interested participants signed the consent documents, completed screening forms, and received a US$5 grocery store gift card as a token of appreciation for their time and interest. Research staff were available during the screening process to answer questions and assist older adults as needed. This multifaceted recruitment approach proved effective in ensuring thorough participant engagement and enrollment.

#### Inclusion and Exclusion Criteria

Older adults with at least one of the following: (1) inadequate or no working technology device (computer, smartphone, or tablet), (2) no or poor internet connectivity at home, and (3) lack of knowledge and usage of technology AND at least one of the following (1) food insecurity or (2) low diet quality, were considered eligible for inclusion in the study. Technical inclusion criteria were measured by questionnaires adapted from the Attitudes Toward Computers Questionnaire and technology use questionnaire from the National Health and Aging Trends Study (NHATS). Food security was assessed using the 10-question US Adult Food Security Survey Module and diet quality was screened using the Dietary Screening Tool [38]. Older adults were excluded from the study if they had a terminal disease or illness, a diagnosis of dementia or Alzheimer disease, or were unable to read or write in English or Spanish.

#### Randomization and Allocation

Twelve out of the 14 centers participated in the study and were stratified by congregate meal participant enrollment and attendance as large (>100 participants), medium (50‐100 participants), and small (<100 participants) and randomly assigned to one of 2 start times: immediately (Cohort 1) or 6 months later (Cohort 2). Site randomization by a statistician occurred after participant recruitment; however, the treatment condition was not revealed to the participants. Neither the study participants nor the study staff were blinded to the treatment conditions.

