#### Statistical Models

##### Aim 1

Primary outcome data will be analyzed in Aim 1. For each of the 3 outcomes in Aim 1 (Dietary Quality Score and Food Security), at 3-month and 6-month periods, a 2-level multilevel model (MLM) will be constructed that examines change over time for individual participants within centers. MLMs consider that participants within a cluster (eg, a center) share characteristics that make them more like each other than participants at other centers. MLM has several distinct advantages over other modeling strategies: (1) MLM has greater statistical power given that the estimated standard errors are corrected for model dependency; (2) there is no need to assume or test for the homoscedasticity or sphericity assumptions, as these variance and covariance components are estimated within the MLM model. Depending on model complexity and whether the statistical assumptions are met, the models will be estimated via Bayesian estimation or maximum likelihood estimation with robust standard errors. For Level 1 (participant level), the outcome variable of interest will be modeled using pretest score on the outcome measure, treatment status (ie, control or experimental), and any nonequivalent baseline participant characteristics as covariates. Level 2 (center level) will model the cluster effect of centers on outcomes.

##### Aim 2

Data collected for Aim 2 represent our secondary research questions (eg, physical activity, technology knowledge and attitudes, social isolation, and loneliness). Data collected at all time points (Physical Activity Scale for the Elderly [PASE], technology knowledge and attitudes, social isolation, and loneliness) will be analyzed using MLM described in Aim 1. To minimize participant fatigue, data for this secondary research aim will be collected at defined intervals (T0, T1, and T2). These data will include the Healthy Eating Index and Short Physical Performance Battery (SPPB) to assess physical function. Differences between groups will be assessed at T2 for each outcome via 2-level covariate MLM models. Level 1 (participant level) will test whether treatment status (ie, control or experimental), pretest score on dietary quality, and food security, and any nonequivalent baseline participant characteristics predict outcomes. At Level 2 (center level), we will model the influence of the 7 centers.

##### Aim 3

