To assess the long-term impacts of the program at T3, Level 1 (time) will model the change in the outcome variables throughout the study (T0, T1, T2, and T3) within each participant. Specifically, each participant’s random intercept (eg, initial status) and the random slope over the 3 time periods will be calculated, and the time variable will represent the change in a particular outcome variable (ie, food security) over time within each participant. Level 2 (time nested within participant characteristics) will test whether treatment status (ie, control or experimental) and any nonequivalent baseline participant characteristics predict outcomes. If the ICC coefficient is greater than 0.10, a third level will be added to the model to control for clustering by center. Finally, participants will be clustered within centers (Level 3).

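### The printed size strata for randomizing the 12 centers overlap, and the stratum appears in none of the Aim 1 to 3 models; the cost is precision, not bias

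*Protocol article*

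**What the plan says.** **Strata.** Under Randomization and Allocation, the 12 participating centers were "stratified by congregate meal participant enrollment and attendance", with the classes "large (>100 participants), medium (50‐100 participants), and small (<100 participants". The same sentence ends the class list and goes on to the allocation, "and small (<100 participants) and randomly assigned to one of 2 start times": immediately (Cohort 1) or 6 months later (Cohort 2). Two size measures are named, with no statement of which one set the class.

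**Models.** Under Statistical Models, the terms are listed aim by aim.
- Aim 1, Level 1: "pretest score on the outcome measure, treatment status (ie, control or experimental), and any nonequivalent baseline participant characteristics as covariates". Level 2: "Level 2 (center level) will model the cluster effect of centers on outcomes".
- Aim 2 has a similar participant-level list, and "At Level 2 (center level), we will model the influence of the 7 centers". Twelve centers were randomized.
- Aim 3: Level 1 is time. Level 2 is the participant and "will test whether treatment status (ie, control or experimental) and any nonequivalent baseline participant characteristics predict outcomes". Center is a third level, described as added if the ICC exceeds 0.10.

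**Imbalance rule.** Under Baseline Equivalency, characteristics at individual and cluster level are compared for imbalance in demographics, baseline dietary intake and food security. Variables with an effect size from .05 to .25 enter the models.

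**The concern.** There are two linked problems. First, the stratum limits are not mutually exclusive, so a reader cannot assign a mid-sized center to a class from the text. Second, the size class constrained the randomization, yet it is not among the model terms that the article lists.

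If size is related to outcome, stratified allocation removes that source of difference between cohorts. A model without the stratum still counts it in the between-center variance. The standard error is then larger than the design warrants, the test rejects too rarely under the null, and power is lost. With 12 centers, between-center variance is estimated on few degrees of freedom, so both the gain from including the stratum and its price need to be worked out.

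**Working it through.** **1. The plan's own figures.** For d = 0.30, two-sided alpha 0.05 (sidedness assumed) and 80% power, n per arm = 2(1.960 + 0.842)²/0.30² = 174.5, so 175 per arm and 350 in total. The t-based version gives 176 per arm, which is the stated 352. Power for d = 0.41 at effective N = 374 is 97.7%, as stated. These figures reproduce without any use of the strata, so adding the stratum does not alter the stated sample size.

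**2. Overlap.** Each whole-number size from 1 to 150 was classified by the printed limits:

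| Size | Classes met |
|---|---|
| 1 to 49 | small |
| 50 to 99 | medium and small |
| 100 | medium |
| above 100 | large |

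Fifty sizes fall in two classes, and only exactly 100 is medium alone. If small meant below 50 (an assumption; the article does not say so), each size would fall in one class.

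**3. Can the stratum enter by another route?** The imbalance rule looks at the cluster level but does not name center size, and the models admit nonequivalent *participant* characteristics. The rule is also triggered by imbalance, which stratification is meant to prevent. A well-balanced stratum would tend to fall below the .05 trigger.

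**4. Size of the precision loss.** Inputs: ICC 0.016 (Power Calculations and Estimation of Sample Size); 398/12 ≈ 33 participants per center; total variance set to 1. The share f of between-center variance explained by size is assumed.

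Variance of a center mean without the stratum: 0.016 + 0.984/33 = 0.0458.
With the stratum: 0.0458 − 0.016f.

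- f = 0.25: 0.0458 − 0.004 = 0.0418; SE ratio √(0.0458/0.0418) = 1.05.
- f = 0.50: 0.0458 − 0.008 = 0.0378; SE ratio √(0.0458/0.0378) = 1.10.

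**5. Price.** Three strata cost 2 of 10 degrees of freedom. t(0.975, 10) = 2.228 and t(0.975, 8) = 2.306, a ratio of 1.035. The net gain in interval width is 1.10/1.035 ≈ 1.06 at f = 0.50, and about 1.01 at f = 0.25. Break-even: 1.035² = 1.071; 0.0458/1.071 = 0.0428; f = (0.0458 − 0.0428)/0.016 ≈ 0.19.

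**6. Simulation.** Assumptions: 12 centers, 4 per stratum, split 2:2; 33 per center; ICC 0.016; d = 0.30; t-test on unadjusted center means; 5,000 runs per setting.

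| Variance explained by size | Type I error without / with stratum | Power without / with stratum |
|---|---|---|
| 0% | 5.3% / 4.9% | 60% / 58% |
| 25% | 3.8% / 4.9% | 59% / 61% |
| 50% | 2.9% / 4.7% | 58% / 64% |
| 75% | 2.1% / 5.1% | 58% / 70% |

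The table compares the two analyses under these assumptions. It does not estimate the trial's own power.

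**The case against.** The strongest reply is that this is a journal article, and that naming stratification factors as covariates is commonly left to the analysis plan. That would answer mere silence. Here the article lists the terms of each model and the stratum is not among them. A fuller plan may add it, but the published specification does not. The overlap stands in any case.

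The next reply concerns size, and much of it stands. No figure in the article says how much of the between-center variance size explains. Below about 19%, adding the stratum widens the interval. The calculation uses an unadjusted center mean, whereas Aim 1 adjusts for the pretest score, which can absorb stable center differences, including those tied to size. The real gain may therefore be smaller than shown.

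Three stronger readings are tempting, and the documents do not support them.
- A reader might infer that the strata are lost. They are not: a statistician has already randomized the sites, so the allocation record should hold the classes used. <100 may be a misprint.
- A reader might infer that every aim has a center effect at Level 2 and nothing else. In Aim 3, Level 2 is the participant and center is a conditional third level. At an ICC near 0.016 that level would not be triggered, and the inflated center variance would not arise in that form.
- A reader might infer that the treatment estimate is biased. Leaving out a stratification factor here makes the test conservative; it does not bias the estimate.

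**Conclusion.** The point holds in a limited form. The overlap of the printed limits is certain. So is the absence of the size stratum from the listed terms in all three aims, with an imbalance rule that is unlikely to bring it in. The consequence is modest and conditional: no bias, but a conservative test and some lost precision if center size predicts outcome.

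At ICC 0.016 and about 33 per center, the net gain in interval width from including the stratum is about 6% if size explains half of the between-center variance, about 1% if it explains a quarter, and negative below about 19%. These figures assume three occupied strata and no pretest adjustment, and they apply most directly to the Aim 1 and Aim 2 comparisons between cohorts. The change is worth making because it is cheap and brings the analysis into line with the randomization, not because the result would otherwise be invalid.

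**What to change.** 1. Correct the stratum limits in Randomization and Allocation to the non-overlapping ones in the allocation record, and state whether enrollment, attendance or a defined combination set the class. A limit of below 50 for small is plausible but must be confirmed there.
2. Add the stratum used at randomization as a fixed center-level covariate: at Level 2 in the Aim 1 and Aim 2 models, and as a center-level covariate in the Aim 3 model whether or not the third level is fitted. If it is left out, say why.

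**Cost.** A wording correction and one three-category covariate already on record; no new data and no change to the stated sample size. The downside is 2 degrees of freedom, and about 2 points of power (60% to 58% in the simulation) if size turns out to be unrelated to outcome.
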